## Air cleaner selection, deployment and monitoring

3

### Air cleaner selection

3.1

PACs were selected from commercially available devices provided by partner companies who participated in this public-private partnership that aimed to expedite the development of advanced air-cleaning technologies and provide empirically grounded feedback to manufacturers on device performance. Partner companies were not involved in execution of the research allocation procedures nor the delineation of the results. Their involvement was restricted to providing installing and maintaining the systems at the selected schools executed in a manner consistent with their normal client operations. Each partner company was aware only of systems installed in its assigned schools and had no knowledge of installations by other partners in the remaining schools. Randomization of PAC types to schools was implemented via an algorithm that weighted selection based on device availability from each partner while ensuring that all partner companies were represented at least once. Allocation was finalized before it was disclosed to participating schools and partner companies. In 29 out of 180 classrooms practical constraints such as device size or noise were considered to accommodate specific classroom preferences expressed by the school. Prior to formal laboratory testing all PACs were evaluated for basic mechanic integrity and classroom feasibility considering manufacturer-reported noise levels typically below 40 dB (Figure 4).

**Figure 4 fig4:**
[figure not shown]
Stepwise screening and selection of mechanical air cleaners (PACs) for the randomized controlled trial. Devices were evaluated for mechanical safety, noise, CADR performance, and size constraints. Non-ceiling-mounted devices were favored for practical reasons; one ceiling-mounted device type was included as it constituted the exclusive device type supplied by this partner company.

PACs included in the cRCT employed different airflow configurations and filtration technologies. All selected devices underwent formal pre-testing in highly controlled laboratory settings at Eindhoven University of Technology (TU/e) with CADR as the primary performance metric following the ANSI/AHAM AC-1 standard procedure (57). Tests were conducted in a standardized 28.4 m^3^ chamber where each device was tested in triplicate under well-mixed conditions. The testing protocol is described in detail elsewhere (58). Subsequent inclusion in the cRCT was limited to devices demonstrating adequate CADR performance noise levels and safety standards. Settings of all devices were adjusted in the cRCT to achieve a comparable CADR of 400–500 m^3^/h which corresponds with approximately a 20% improvement over the required ventilation flow rate performance according to Class B as described in the Dutch program of requirements (PvE) for good indoor environmental quality in schools (15). For one type of PAC two devices were needed to reach the required 400–500 m^3^/h

In addition to performance testing, device safety was a critical selection criterion. Previous work has raised concerns about potential byproducts from some air cleaning technologies. Ionization (59–62) and plasma devices (63–66) may generate ozone, which may react with common indoor volatile organic compounds (VOCs) to form secondary byproducts such as formaldehyde and ultrafine particles (59), potentially posing respiratory health risks. Based on these considerations, prior to deployment all units underwent supplementary ozone testing using an Aeroqual device equipped with ozone sensor. Measured ozone concentrations were below detection limits, suggesting formation of secondary reactive species via ozone-mediated pathways is likely minimal.

During the initial study phase (Dec 2023–May 2024), some oversized units were trialed, but based on feedback from schools regarding classroom practicality, these were excluded from the larger cRCT.

### Air cleaner deployment and monitoring

3.2

PACs were intended to be positioned according to the partner companies’ recommendations for optimal cleaning efficiency which varied between devices due to differences in airflow configuration and design. However in practice placement was largely dictated by practical constraints such as available space classroom layout and to a minor extent by availability of power outlets. Consequently PAC placement was not fully standardized across classrooms but rather reflected realistic implementation conditions in occupied school environments. Teachers were instructed to keep the devices operational at all times and asked to document any temporary shutdowns or adjustments to lower settings on a standardized log form. Beyond this schools could continue their usual routines and no modifications to ventilation practices were instructed. In addition during each three-week routine sample collection (described below) the operational status and settings of the devices were systematically recorded by the research team. For schools using the PACs over extended periods devices requiring maintenance were attended to after the summer holiday following the manufacturer’s standard procedures to ensure consistent performance. Additionally TU/e conducted follow-up performance testing of all devices at the end of the study period to verify sustained air cleaning efficacy. Blinding of students and school staff was not feasible as air cleaners without active filtration could not be provided across all participating partner companies.

## Sample collection and measurements

4

### Airborne dust sampling

4.1

Airborne dust was passively collected using electrostatic dust fall collectors (EDCs) following the standardized protocol by Noss et al. (67). Each EDC consisted of two electrostatic cloths (purchased from Albert Heijn, The Netherlands) which were sterilized by heating at 220 °C for 4 h enclosed in an ethanol-cleaned polypropylene folder. Prior to deployment, EDCs were packaged in closed bags. EDCs were typically suspended from the classroom ceiling (> 0.3 m below ceiling, ≥ 1.80 m above floor surface), positioned centrally and away from windows, doors, PACs, lighting fixtures, and ventilation inlets/outlets. In a subset of classrooms (19 of 180), placement was adapted due to practical constraints. In most of these cases (15 of 19), the adapted placement was approximately standardized within classroom clusters, such that all classrooms within a cluster used similar EDC positioning. Samplers were exposed for three-week intervals over one baseline and three consecutive repeated intervention measurements, resulting in a total sampling period of 12 weeks for the EDCs (Figure 1). To monitor background contamination, sealed field blanks (32 initial phase, 113 main study) and laboratory blanks (38 initial phase, 77 main study) were included.

### Laboratory analysis and microbial targets

4.2

Following sample collection, EDC cloths were removed from the holders individually packed in bags and stored at −80 °C until Deoxyribonucleic acid (DNA) and ribonucleic acid (RNA) extraction. Samples were thawed, mixed with 10 mL of 1:1 LGC lysis buffer BL (LGC Genomics GmbH) and Phosphate Buffered Saline (PBS; Gibco™ 1 × Dulbecco’s phosphate-buffered saline without calcium, magnesium, and phenol red; Fisher Scientific), agitated on a roller for 30 min, and placed on ice. Bacterial and viral targets were extracted from 350 μL of supernatant using commercially available kits (see Supplementary Table S2 for detailed reagent information): the LGC DNA kit [LGC Genomics GmbH; per Fakunle et al. (68)] was used to extract total nucleic acids (DNA and RNA), while the Zymo Quick-RNA MiniPrep Kit (Zymo Research, supplied by Sanbio) was used to extract RNA with DNA removal, according to supplier instructions.

Bacterial and viral targets were analyzed in technical duplicates, respectively, by qPCR and reverse transcript qPCR on a BioRad CFX 384 (initial phase) or QuantStudio (main phase) machine with negative controls and 50 PCR cycles (see Supplementary Table S3 for detailed assay conditions). Standard curves of synthesized gBlock fragments were included to enable quantification. Quality-control checks will report blank contamination (counts, percent detectable, and mean blank levels) and duplicate agreement (mean difference, limits of agreement, correlation metrics); handling of any background contamination will be described. Limits of detection (LOD) and quantification (LOQ) will be reported. Laboratory personnel were blinded to intervention allocation.

Bacterial targets (*Staphylococcus aureus*, *Streptococcus salivarius*, *Staphylococcus epidermidis*, and *Moraxella catarrhalis)* represent common constituents of the human microbiome across the respiratory tract, mouth and skin. Viral targets (respiratory syncytial virus (RSV), Influenza A and B) were selected as representative agents of prevalent seasonal respiratory infections. Although the study was initially conceptualized in the context of COVID-19, SARS-CoV-2 was not included due to challenges in consistent airborne detection at the time of the field study, and to broaden the scope toward airborne microbial exposure and infection prevention more generally.

### Active air sampling sub-study

4.3

To complement passive dust collection, active air sampling was conducted in a sub-study to support quantification and validation. In a subset of 12 classrooms at one school, active air sampling was performed using Derenda pumps equipped with Harvard impactors and Teflon filters (Pall 2.0 um pore-size), operated continuously at 0.20 m^3^/h, in parallel with passive sampling to allow validation and quantification of EDC measurements.

### Physicochemical markers

4.4

Low-cost indoor air quality sensors were used for continuous monitoring at one-minute intervals of PM₁₀, PM₄, PM₂.₅, PM₁, CO₂, air temperature, relative humidity, and volatile organic compounds (VOCs). Each sensor integrated a Sensirion SPS30 particulate matter sensor for both mass and number concentrations (69), a MH-Z19-C non-dispersive infrared (NDIR) CO₂ sensor (70), either an AM2320 or ENS210 air temperature/humidity sensor (71, 72), and a Renesas ZMOD4410 sensor for total VOC (TVOC) and ethanol-equivalent concentrations (73). The MH-Z19-C sensor applies an automatic baseline calibration (ABC) algorithm, which stabilizes CO₂ measurements within approximately 1 week after installation by periodically adjusting the sensor baseline based on minimum nighttime concentrations.

Upon receipt from the supplier and prior to deployment, all sensors were checked and compared to research grade instruments. All sensor units were tested side-by-side in batches of approximately 30 sensors under controlled indoor conditions for ~4.5 h and compared against a Grimm 11-D particle sensor (74) for particulate matter measurements and a Vaisala HMP1 (75) for CO₂, air temperature, and relative humidity measurements. Sensors showing unstable signals, substantial deviation from reference measurements, communication issues, or other malfunctioning behavior were considered unreliable and excluded from the study.

In 165 out of 180 classrooms, two sensor units were installed per classroom on opposite sides of the room to capture potential spatial variability and ensure redundancy in case of device failure or disconnection. Sensors were deployed continuously during the 9-week intervention period and for an additional 2-week pre- or post-intervention period, resulting in a total monitoring duration of 11 weeks per classroom. Classroom ventilation was estimated with the average air change rate (ACH) calculated from CO₂ decay curves, applying the standard exponential decay method following source removal (76). A running window was applied to identify CO_2_-decay curves during the monitoring period from which ACH could be derived.

### Environmental and health monitoring

4.5

Contextual data will be considered to aid interpretation of observed airborne microbial and PM measurements, including weekly national infectious-disease surveillance reports (77–79), as well as ambient PM and NO₂ data obtained from national monitoring networks, with outdoor NO₂ used as an indicator of traffic-related pollution that may influence indoor PM levels (80). Classroom-level absenteeism (anonymized) was recorded. Parent-reported respiratory symptoms, including wheezing, asthma, allergic complaints, and respiratory infections, were collected via retrospectively administered surveys at the end of the 2024–2025 winter season. Two surveys were administered, covering respiratory symptoms during the winters of 2023–2024 and 2024–2025, respectively. Depending on the school, the 2023–2024 winter represented either a pre-intervention or an intervention period. The questionnaire was adapted from a previous survey (81), which included selected items from the International Study of Asthma and Allergies in Childhood (ISAAC) questionnaire (82). Survey data were pseudonymized prior to analysis. Detailed descriptions of the survey and epidemiological analysis will be reported in future work.

The simulations, which considered different assumptions about variance and the number of classrooms per school, indicated that achieving 80% power could require between 6 and 25 schools, depending on whether schools contributed 1, 2, or 3 classroom clusters (see Supplementary Table S4; Supplementary Figures S1, S2 for details). Results indicated that including two clusters per school rather than one substantially increased power, whereas adding a third cluster per school had a smaller additional effect. Increasing the number of repeated measurements per classroom from three to four also increased power modestly. Including an additional baseline measurement prior to intervention further increased power. Based on these simulations the study design included a baseline measurement plus three repeated intervention measurements per classroom.

## Data analysis plan

6

All analyses will be performed in RStudio [version 4.5.1 (83)]. The project will use the UU network drive for secure data archiving, with access restricted to authorized study personnel. Data were coded using consistent study identifiers prior to analysis, with a separate pseudonymization key linking identifiers to study sites.

Intervention effects taking into account data of all participating schools will be assessed using generalized linear mixed-effects models (GLMMs) with random intercepts for school, cluster, and classroom, reflecting the hierarchical clustering inherent to the study design. Residual normality and homoscedasticity will be verified, applying log transformation when necessary to meet model assumptions. To account for temporal correlation between successive intervention periods within classrooms, autoregressive structures [e.g., AR (1)] will be considered, with their inclusion guided by both model fit and the anticipated influence of seasonal variation. Potential covariates, including grade, classroom dimensions, number of students, student density, lesson hours, floor level, urbanization, ventilation type, and flooring type will be evaluated in univariate GLMMs containing intervention arms and random effects. Covariates significantly impacting intervention estimates or model fit may be considered for inclusion in the final multivariable model, guided by both statistical evidence and conceptual relevance. ACH will be considered as a potential covariate in the mixed-effects models to account for differences in baseline ventilation and may be evaluated as a continuous variable or categorized into predefined ranges (ACH-bins). Multicollinearity will be assessed, with highly correlated variables excluded to ensure model stability, and the final model will be selected based on overall fit (AIC, likelihood ratio tests).

Sensitivity analyses will assess model robustness by re-fitting the final models after exclusion of outliers (identified by influence diagnostics), exclusion of baseline measurements, and restriction to the 2024–2025 sampling period only. An additional sensitivity analysis will be performed to assess the robustness of the findings under protocol-compliant PAC operation. Only measurements without indication of incorrect PAC operation are included, based on the recorded device settings during sample placement and collection by the research team and the absence of reported deviations in the teacher log forms.

Data analysis of species-specific bacterial and viral markers will be guided by observed detection levels. Where quantitative measurements permit, marker concentrations will be analyzed using GLMMs as described above. If detection within the quantifiable range is limited, outcomes will be modeled as binary (detected or non-detected) using logistic mixed-effects models with random effects for school, cluster, and classroom, and fixed effects for the intervention arms. Appropriate model assumptions and hierarchical variance structures will be considered. Correlations between markers may be examined to explore co-detection patterns. Missing data will not be imputed; analyses will use available data within mixed-effects models.

In addition to standard GLMM or binary logistic mixed-effects models, Bayesian hierarchical models may be applied to species-specific outcomes as continuous variables, allowing incorporation of observations outside the quantifiable range while still leveraging the information from measurable values. Observations within the quantifiable range will be treated as measured values, whereas non-detects or values outside of the quantifiable range, will be incorporated as censored data, reflecting the uncertainty in the true underlying value. Feasibility of using a Bayesian approach in this case depends on sufficient informative observations within the measurable range. Random intercepts for school, cluster and classroom will account for the hierarchical structure. Priors for intercepts, intervention effects, residual variance, and group-level variance will be informed by plausible ranges derived from the quantifiable data. Model fit will be evaluated via posterior predictive checks, and sensitivity analyses may explore the impact of prior choices and censoring assumptions.

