## Discussion

7

This cRCT study design intends to evaluate PAC effectiveness in primary school classrooms under real-world conditions while preserving methodological rigor. Compared with laboratory-based studies, this field-based approach strengthens validity by reflecting real classroom dynamics, including occupant behavior, ventilation variability and practical use of PACs. The study will employ a dual-control design (Figure 1), that will combine measurements in all classrooms during a non-intervention period as well as control classrooms throughout the study. This design enables differentiation between pre-existing classroom differences and temporal trends. Although not blinding students and school staff to PAC placement may have introduced some behavioral changes. Repeated measurements enhance statistical power and temporal resolution. Clustering classrooms by key characteristics improves comparability between intervention and control groups. Random allocation of intervention arms minimizes allocation bias, although perfect comparability between classrooms within a cluster is unattainable.

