The distribution of ventilation types in participating schools (3.7% balanced mechanical, 11.1% mechanical exhaust only, 74.1% mechanical (type unknown), 11.1% natural) suggests a higher prevalence of mechanically ventilated classrooms compared with the national snapshot reported by Krishnan et al. (88), who found 40% natural, 16% fully mechanical systems, 4% mechanical supply only and 40% mechanical exhaust only across 25 Dutch school buildings. However, self-reported ventilation types may not reliably reflect actual performance, as schools may not be fully aware of system operational status and maintenance. To evaluate the ventilation performance in classrooms, ACH will be determined from the CO₂ decay curves. As ventilation conditions may influence PAC effects, with greater effects generally observed at lower ventilation rates (89, 90), the planned analyses may account for differences in baseline ventilation by adjusting for ACH.

To monitor airborne microbial exposure, EDCs were employed. EDCs enable low-cost, silent, and electricity-free sampling, facilitating standardized deployment on a large scale over extended periods without disrupting teaching activities. While EDCs provide integrated rather than real-time measurements, they are well-established for monitoring airborne microbial material, such as endotoxins (67, 91–93), bacterial (94–97) and viral (98) particles, with moderate to strong correlations to active samplers (r ≈ 0.54–0.84) in household and farm environments (67, 93, 95). Viral detection with passive samplers may remain challenging due to low viral prevalence and inherent variability in classrooms (99), whereas bacterial and 16S markers are more consistently measurable and provide a proxy for airborne microbial exposure (94–97). While spatial heterogeneity within classrooms, influenced by non-homogeneous air mixing, has been observed empirically and supported by both standard and AI-trained simulations (100–102), sampling was designed to capture representative locations, allowing estimation of average classroom exposure and meaningful comparisons between intervention and control classrooms. Preliminary testing indicated that, while occasional deviations in EDC placement occurred due to practical constraints (e.g., ceiling height), placement was generally consistent within clusters. Overall, EDCs offer a feasible, reproducible, and minimally disruptive approach for large-scale classroom airborne microbial monitoring.

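### The air change rate offered as a baseline-ventilation covariate is measured mostly during the intervention, so adjusting for it can change the effect being estimated, and it does not address effect modification

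*Protocol article*

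**What the plan says.** Section 6 (Data analysis plan) lists ACH as an optional covariate: "ACH will be considered as a potential covariate in the mixed-effects models to account for differences in baseline ventilation". It may enter as a continuous variable or in bins. For covariates generally, the section gives weight to those that move the intervention estimate or improve fit, and it selects the final model by AIC and likelihood ratio tests.

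Section 4.4 (Physicochemical markers) says how ACH is obtained: "Classroom ventilation was estimated with the average air change rate (ACH) calculated from CO₂ decay curves". A running window identifies CO₂ "decay curves during the monitoring period from which ACH could be derived". On timing: "Sensors were deployed continuously during the 9-week intervention period and for an additional 2-week pre- or post-intervention period". The section puts the total at 11 weeks for each room. It also says that the CO₂ sensor's self-calibration "stabilizes CO₂ measurements within approximately 1 week after installation".

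Section 3.2 says that students and staff could not be blinded, that schools kept their usual routines, and that no change to ventilation practice was instructed. Section 7 (Discussion) adds: "Although not blinding students and school staff to PAC placement may have introduced some behavioral changes". It also notes that air cleaners tend to have larger effects where ventilation is low, and concludes that "the planned analyses may account for differences in baseline ventilation by adjusting for ACH".

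**The concern.** Two things do not fit together.

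First, the covariate is called baseline ventilation, but the only derivation given covers the whole monitoring period, which is mostly intervention time. Nothing restricts it to weeks with the devices off. Ventilation in those weeks can respond to a visible device in the room. Conditioning on it blocks one route by which the intervention acts in practice. Section 7 presents occupant behaviour and ventilation variability as part of the real-world conditions under which effectiveness is to be judged.

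Second, the reason given for adjusting is that the effect differs by ventilation level. That is a statement about an interaction. A main-effect ACH term, continuous or binned, still yields one common intervention effect.

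The selection rule adds to the problem. If it is applied to ACH, a covariate that moves the intervention estimate becomes a candidate for inclusion. ACH that has shifted by arm would do exactly that.

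**Working it through.** **Share of the window.** The plan's figure reproduces: 9 + 2 = 11 weeks. Intervention share: 9/11 = 81.8%. Off share: 2/11 = 18.2%. Where the two off weeks come first and about one week is lost to sensor settling, roughly 1 of 10 stable weeks (10%) precedes the intervention. Where they come last, none does. The article does not say how many rooms fall in each group.

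**Inputs from the document.** Clean air delivery rate (CADR) 400–500 m³/h, midpoint 450 (Section 3.1). Median volume V = 156.2 m³ and median 24 students (Table 2, main phase). Required ventilation 6 dm³/s per person (Introduction).

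- Reference ACH: A = 6 × 3.6 × 24 / 156.2 = 3.32 per hour.
- Device removal rate: P = 450 / 156.2 = 2.88 per hour.

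**Assumptions not in the document.** A well-mixed room at steady state without deposition, so concentration is proportional to 1/(ACH + P); ventilation in device rooms changes by a fraction d while devices run, with d from −20% to +20%.

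- Effect at fixed ventilation: 1 − A/(A + P) = 1 − 3.32/6.20 = 46.5%.
- Total effect: 1 − A/(A(1 + d) + P). For d = −20%: 1 − 3.32/(2.66 + 2.88) = 40.0%. For d = +20%: 1 − 3.32/(3.98 + 2.88) = 51.6%.

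**Regression check.** Log concentration was simulated for a large number of rooms, two thirds with devices (assumed SD of log ACH between rooms 0.4, residual SD 0.6). It was regressed on arm alone, then on arm plus log ACH averaged over 9 on-weeks and 2 off-weeks.

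| Change in ACH | Total effect | Adjusted for 11-week ACH | Adjusted minus total |
|---|---|---|---|
| −20% | 41.2% | 47.7% | +6.5 points |
| −10% | 44.7% | 47.8% | +3.1 |
| 0 | 47.5% | 47.5% | 0 |
| +10% | 50.3% | 47.5% | −2.8 |
| +20% | 52.5% | 47.2% | −5.3 |

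Adjusting instead for pre-device ACH gives 41.2%, 44.7%, 47.5%, 50.3% and 52.6%, which is the total effect.

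**Range (closed form, d = −20% / +20%).**

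- Starting ACH 1.5 per hour: 65.8% at fixed ventilation; total 63.2% / 68.0%; gaps 2.6 and 2.2 points.
- Starting ACH 6 per hour: 32.4%; total 21.9% / 40.5%; gaps 10.5 and 8.1 points.
- Reference ACH with an added deposition loss of 1 per hour: 40.0%; total 33.9% / 45.1%; gaps 6.1 and 5.1 points.
- Device effect at fixed ventilation equal to the 20% design target (Section 5), so P = 0.25A: total 1 − 1/1.05 = 4.8% / 1 − 1/1.45 = 31.0%; gaps 15.2 and 11.0 points.

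**Effect modification.** In the same model the reduction P/(A + P) is 65.8% at ACH 1.5, 46.5% at 3.32 and 32.4% at 6 per hour. A model with only a main effect of ACH reports a single figure for all three.

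**The case against.** The strongest reply has five parts.

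- **Adjustment is optional.** The article says ACH will be considered and that analyses may adjust for it. A reader might infer that the adjustment is fixed; it is not. This stands, but the selection rule makes inclusion more likely when ACH has shifted by arm.
- **The devices do not themselves alter CO₂.** Nothing in the article says they do, so ACH moves only if people ventilate differently. A reader might infer that adjustment necessarily removes part of the benefit. The documents do not support that: with unchanged behaviour there is no bias, and otherwise either direction is possible. Section 7 concedes that behaviour may have changed. It does not say that change is expected, and it does not mention ventilation.
- **Decay curves are taken after occupants leave, and 88.9% of main-phase classrooms are recorded as mechanically ventilated (3.7 + 74.1 + 11.1).** Both may weaken the window-opening route. This stands in part. Section 7 itself doubts self-reported ventilation types, and 74.1% are of unknown type.
- **The covariate's window may be settled in the full plan.** That could be so. But the article gives one derivation and one label, and they conflict. The 82% follows the stated schedule and is not universal: initial-phase schools had one to four intervention periods, and control rooms never had a device.
- **The size is assumed.** A 20% change has no source in the document. A reader might also compute a larger gap. With ACH 3.5 per hour falling to 2.8, the total effect is 1 − 3.5/5.68 = 38%, against 1 − 2.8/5.68 = 51%, or 13 points. That evaluates the fixed-ventilation effect at the reduced rate. At the original rate it is 1 − 3.5/6.38 = 45%, a gap of about 7 points, and the simulated adjusted estimate agrees with this placement.

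**Conclusion.** The point holds in a conditional form. ACH as derived in Section 4.4 is a post-randomisation variable in unblinded classrooms and should not be treated as baseline. Adjusting for it moves the target from the total real-world effect to the effect at fixed ventilation. At the document's median room, and with an assumed 20% ventilation change, the adjusted estimate is about 6 to 7 points too high if device rooms ventilate less and about 5 points too low if they ventilate more. It is correct if ventilation does not change. Over starting ACH of 1.5 to 6 per hour the gap runs from about 2 to about 10 points, and it would be larger for a weak device effect near the 20% design target. All of these figures rest on the well-mixed model and the assumed behaviour change.

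The second part needs no such assumption: the rationale in Section 7 concerns effect modification, and the adjustment it names cannot show it.

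**What to change.** 1. Estimate the main intervention effect without on-period ACH, and exempt ACH from the data-driven covariate rule.
2. If ventilation is adjusted for, compute ACH only from device-off weeks. Prefer pre-intervention weeks after the roughly one-week sensor settling time. Flag rooms that have only post-intervention weeks: that ACH is device-off but not a true baseline.
3. Pre-specify an arm-by-device-off-ACH interaction as the effect-modification analysis.
4. Report on-period ACH by arm, to show whether ventilation behaviour changed. Label any model adjusted for on-period ACH as a sensitivity or mediation analysis.

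The cost is revised wording and re-tabulation of CO₂ data already collected. Device-off ACH rests on fewer decay curves, and Section 2.1 itself notes seasonal differences in ventilation behaviour, so it may not represent ventilation in other seasons. The adjustment and the interaction will therefore be less precise.
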